#### **7.1.5. Primary Endpoint Aim 3**

Consistent with the primary Aim 3 hypothesis, that women who receive Glow/GC will be less likely than women who receive CPSP/IC to have a preterm birth, the following endpoint will be assessed from the delivery medical record review.

- Whether the participant had a baby born less than 37 weeks gestation, as noted in the participant's medical record.

#### **7.1.6. Secondary Endpoint Aim 3**

Consistent with the secondary Aim 3 hypothesis, that women who receive Glow/GC will have babies born at higher gestational ages than women who receive CPSP/IC, the following endpoint will be assessed from the delivery medical record review.

- The gestational age at which the baby was born (number of weeks), as noted in the participant's medical record.

## **7.2 Sample Size**

We conducted sample size calculations for change in depressive symptom severity. We powered our study to detect meaningful changes in depressive and anxiety symptoms. Using an alpha of .05 and power of .85, we will be able to detect a standardized effect size of 0.25 with a sample size of 578 individuals in total (289 per arm). We are assuming a retention rate of 88% (as per our previous study and experience in the current study) and power of 85% (per PCORI's request). A standardized effect size of 0.2 to 0.3 is widely considered to be a small effect size. We therefore plan to enroll 657 participants in the study, and, with a retention rate of 88%, we will have > 85% power to detect small effect sizes for these outcomes. Adjustment for covariates in multivariable analyses for numeric outcomes may make the residual SD smaller than the raw SD, improving precision and power.

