## **2.2 Study Design**

This is a randomized comparative effectiveness trial to determine the effect of two enhanced prenatal care models, Glow/GC and CPSP/IC, on depressive and anxiety symptom severity; person-centered care, perceptions of respectful care, and satisfaction with prenatal care; and PTB rates and gestational age at delivery among 657 birthing people. Providers will be randomized to the order in which they offer the two models, and participants will be allocated to each of the comparators based on their provider and expected due date. Providers may select the mode of comparator delivery—either in person, via telehealth or a combination of both—according to personal preferences, health center regulations, and local public health guidelines. A CONSORT diagram of the study is presented as Figure 2.

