## 4.0 STUDY ARMS

### 4.1 Glow/GC (enhanced group prenatal care, eGPC)

Glow/GC, Comparator 1 for this study, is an enhanced group prenatal care program administered by First 5 Fresno County that offers co-located social services provided by established community agencies with independent funding streams targeting low-income families. The Glow/GC model pairs a trained staff facilitator with a licensed prenatal care provider from a practice site to provide billable prenatal care to the practice's own patients. Over the course of 8-11 sessions, 6-12 women (within a 6-week gestational age range) receive prenatal and postpartum medical care, risk assessments, social support, and gain knowledge and skills related to pregnancy, birth, and parenting. Glow/GC modifies the CenteringPregnancy®69 curriculum, which incorporates ACOG recommendations for prenatal

care, to include modules focusing on depression, anxiety, sleep, mindfulness, and how discrimination may affect birth outcomes. Spanish-language sessions and materials are available.

Additional Glow program components include childcare support with developmental assessments (in-person model) or in-home early learning activities for children ages 0 to 5 (telehealth model); education, referral, and treatment for perinatal mental health issues and conditions administered by the Department of Behavioral Health, Perinatal Wellness Program (both models); transportation stipends (both models); take-home food (in-person model) or food delivery (telehealth model) through local food banks and other community agencies; and direct coordination/enrollment with education, housing, economic assistance, and other local services as needed (both models). Glow/GC staff maintain a county-based, low-income resource guide and work continuously to build relationships and facilitate warm handoffs.

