**Aim 3 Hypotheses (exploratory):** Women assigned to Glow/GC will have lower rates of preterm birth (**primary (1°)**) and will give birth at higher gestational ages (**secondary (2°)**) than women assigned to CPSP/IC.

**Aim 3 Analyses:** We will describe simple differences in proportions of preterm birth and mean gestational age by treatment group. We will examine models comparing treatment assignment to Glow/GC versus CPSP/IC including the covariates, using logistic mixed models (for preterm birth) and linear mixed models (for gestational age), with clustering by practice and provider. We will examine assumptions of normality for the gestational age outcome, and deviations from linearity for covariates. **Exploratory subanalyses (3a):** We will explore preterm birth rates and gestational age at delivery among Black and Latina participants in each treatment arm, to examine whether Glow/GC and CPSP/IC may be more or less effective in these subgroups. These aims will be exploratory in nature, as we do not anticipate having a sufficient sample to have high power to test our hypotheses in these groups. We will assess effectiveness within subgroups based on race/ethnicity and language and report the p-value for interaction.

We will begin to code data immediately after the first phase of interviews are completed, in bimonthly data meetings that will include interview staff and co-investigators. We will take extensive notes during meetings to document emergent concepts and themes for codebook development. Codes will be developed mirroring the topics outlined in interview guides, which we will develop prior to study initiation. Regular data analysis meetings will create a constructive dialogue that both triangulate the quantitative and qualitative data collected in Aim 2. While reviewing qualitative data, we will note reoccurring themes (open coding). While completing open coding, we will write theoretical and methodological memos consistent with qualitative analysis methodologies. We will finalize a codebook and code and enter all data into Dedoose. We will review selected transcripts to check for inter-coder reliability. Staff will maintain the coding database and produce outputs for analysis and generate data summaries.

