*Missing outcomes and covariates:* As baseline data will be collected at time of treatment assignment, and clinical outcomes will be obtained from medical record review, we do not estimate substantial missing data for Aim 3. We plan to reduce missing data for Aims 1 and 2 through our retention plan. We will record all reasons for study withdrawal and missing data. Participants lost-to-follow up will undergo medical record review for the outcomes of preterm birth and gestational age. Our mixed model analyses offer robust protection against data that are missing at random. We will assess missing data across study covariates and time points and use multiple imputation if it is appreciable. Pregnancies that end in miscarriage, abortion or fetal death prior to 20 weeks gestation will not be included in analysis.

*Heterogeneity of treatment effect (HTE):* We will assess if the effectiveness of Glow/GC compared with CPSP/IC differs by practice or patient characteristics through interaction analyses. Pre-specified analyses of treatment heterogeneity include: complications of pregnancy, parity, race/ethnicity, provider type (CNM, MD, NP). We will also conduct exploratory analyses on additional covariates (social support, site, size of practice or location, prior experiences of racism) to assess treatment differences. HTE will be assessed using interactions between

treatment assignment and each proposed effect modifier tested with a cut-point of ( $p < .10$ ) for HTE.

*Avoidance of bias:* The use of randomization of treatment initiation within practices allows us to minimize the risks of confounding and selection bias. More efficient designs with less susceptibility to bias are unfortunately not feasible in this study, as the treatment is administered at the practice level and needs to be incorporated without substantial interruption to clinical processes. To enhance generalizability of the study, we are recruiting from a diverse low-income patient population including English- and Spanish-speakers, with study staff and all assessment tools available in both languages. While we cannot mask treatment assignment to providers, participants or study staff, we will make every effort to ensure equivalent study procedures across both groups. Chart review and data analysis will be performed by study staff masked to treatment assignment to reduce ascertainment bias.

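### The claim of more than 85% power for small effects is wrong as written: it fails below d = 0.25 and leaves no margin for clustering

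*Combined protocol and SAP*

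**What the plan says.** Section 7.2 bases the sample size on the Aim 1 primary outcome: "We conducted sample size calculations for change in depressive symptom severity". The inputs are given as "Using an alpha of .05 and power of .85", which the plan says will "detect a standardized effect size of 0.25 with a sample size of 578 individuals in total (289 per arm"). Dividing by 88% retention gives 657 to enrol. The same paragraph calls 0.2 to 0.3 a small effect and concludes that "with a retention rate of 88%, we will have > 85% power to detect small effect sizes for these outcomes". It adds that covariate adjustment may reduce the residual SD, but gives no figure. It states no ICC, design effect, cluster size or number of providers.

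Other sections describe a design in which women are not individually randomised. Section 2.2 says that "participants will be allocated to each of the comparators based on their provider and expected due date". Section 2.3 has each provider alternate between the two arms by six-week due-date window. In Section 4.1, Glow is a shared programme in which "6-12 women (within a 6-week gestational age range) receive prenatal and postpartum medical care". In Section 7.5, the Aim 3 models are fitted "with clustering by practice and provider". The Aim 1 text there says only that linear mixed models will be used, and refers to a plan similar to Aim 1's own.

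**The concern.** There are two separate difficulties. First, the conclusion is about small effects as a class, while the calculation supports one point within the plan's definition of that class. Second, the calculation takes every woman's outcome as independent, while the design gives two reasons for correlation: shared assignment by provider and window, and shared care within a Glow group. Section 1.1.1 counts peer-to-peer processes among the routes by which Glow is expected to work, so some correlation of mood scores within a group is plausible.

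This is the power statement for the primary endpoint, and Section 7.2 says that the 85% was set at the funder's request. If it stands, a null result may be described as coming from a trial with better than 85% power for any small effect. That is untrue at 0.20 and unproven at 0.25.

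**Working it through.** **Inputs.** From Section 7.2: alpha 0.05, power 0.85, d = 0.25, 289 per arm, 88% retention, 657 enrolled, small = 0.2 to 0.3. From Section 4.1: Glow groups of 6 to 12. Section 7.2 does not say whether the test is one- or two-sided; two-sided is inferred because it reproduces the stated number (one-sided needs only 231 per arm). The ICC is not in the documents; 0.01 to 0.05 is assumed here.

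**Step 1: reproduce the plan's figure.** Independent observations, normal approximation: n per arm = 2(1.960 + 1.036)² / 0.25² = 287.3, so 288. With the noncentral t distribution, power is 85.0% (0.8497) at 288 per arm and 85.1% at 289. Enrolment: 578 / 0.88 = 656.8, so 657. The stated figures are therefore the independent two-sample answer, with no design effect in them.

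**Step 2: power across the plan's own range of small effects.** 289 per arm, two-sided, no clustering:

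| d | Power |
|---|---|
| 0.20 | 67.0% |
| 0.22 | 75.2% |
| 0.25 | 85.1% |
| 0.30 | 95.0% |

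**Step 3: the margin.** 657 × 0.88 = 578.2, so no women are in reserve. Power at d = 0.25 drops below 85% once the net design effect exceeds about 1.003 (289 / 1.003 ≈ 288 effective per arm).

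**Step 4: clustering in the Glow arm only.** With m study women per group, the Glow variance is multiplied by 1 + (m − 1) × ICC and the other arm's is unchanged. The average factor is DE = 1 + (m − 1) × ICC / 2. Effective n per arm is 289 / DE, and the effect detectable at 85% power is 0.2497 × √DE.

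| m | ICC | DE | Power at 0.25 | Detectable d |
|---|---|---|---|---|
| 2 | 0.01 | 1.005 | 84.9% | 0.250 |
| 2 | 0.05 | 1.025 | 84.2% | 0.253 |
| 4 | 0.01 | 1.015 | 84.6% | 0.252 |
| 4 | 0.05 | 1.075 | 82.5% | 0.259 |
| 6 | 0.01 | 1.025 | 84.2% | 0.253 |
| 6 | 0.05 | 1.125 | 80.7% | 0.265 |
| 12 | 0.01 | 1.055 | 83.2% | 0.256 |
| 12 | 0.05 | 1.275 | 75.7% | 0.282 |

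**Step 5: allow for providers alternating arms.** For correlation that comes from the provider and window rather than from the Glow group, the cluster-crossover factor is DE = 1 + (m − 1) × ICC − m × ICC × CAC. CAC is the correlation of a provider's effect between windows, and is also an assumption. At m = 12 and ICC 0.05:

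- CAC 1: DE = 1 + 0.55 − 0.60 = 0.95, power 86.8%
- CAC 0.8: DE = 1.07, power 82.6%
- CAC 0.5: DE = 1.25, power 76.5%

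A fully stable provider effect thus costs nothing and even helps slightly. A window-specific effect does cost power.

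**Step 6: how many study women share a cell.** Section 7.3 gives 10 sites, and the schema has data collection from November 2019 to December 2024. Five years of six-week windows is about 5 × 52 / 6 ≈ 43. With one provider per site, that is about 430 provider-windows, and 657 / 430 ≈ 1.5 women in each. If only half were active, the figure is about 3. The number of providers and their active periods are not documented, and uneven cells raise the effective size.

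**The case against.** The best defence is that the arithmetic is correct and the clustering loss may be slight. Both comparators run within each site and each provider alternates, so stable provider and site effects largely cancel (Step 5). The 6 to 12 in Section 4.1 is the size of a Glow group, and the documents do not say that every member is a study participant; the rough count points to 2 to 4. CPSP women have individual care and share no group. Covariate adjustment could also offset a modest design effect: the variance that must be explained is about 1 − 1/DE, which is 7% at DE 1.075 and 22% at DE 1.275. Section 7.5 promises confidence intervals, so a null result need not be read from planned power alone. All of this stands, and it limits the second part of the point.

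It does not rescue the sentence at 0.20. To reach 85% there, covariates would have to explain about 1 − (0.20 / 0.2497)² = 36% of the variance, and Section 7.2 claims no such figure.

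A reader might infer more than the documents allow:

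- **That the design definitely lacks 85% power at 0.25.** This needs an ICC that is not given, and a stable provider effect could leave power slightly above 85%.
- **That power is about 67% at 0.25.** This needs 12 study women per cell in both arms, ICC 0.05 and no carry-over of provider effects between windows (DE = 1.55). It ignores the alternation.
- **That losses before 20 weeks lower power further.** Section 7.5 does say that "Pregnancies that end in miscarriage, abortion or fetal death prior to 20 weeks gestation will not be included in analysis", but the 88% rests partly on experience in this study and may already include them. If they were extra, a 2% to 3% loss would cost about one point.

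**Conclusion.** Wrong as written. That more than 85% power is available for small effects is untrue for the lower half of the range that the plan itself calls small: 67% at 0.20, and 85% only from about 0.25 upward. This rests on the plan's own inputs and a two-sided test.

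At 0.25 the figure is unsupported rather than disproved. It assumes independence that the design does not provide, and it has no margin. With Glow-arm clustering only and an assumed ICC of 0.01 to 0.05, power is 82.5% to 84.9% for 2 to 4 study women per group, and about 76% to 84% for 6 to 12. The smaller groups fit the rough count from sites and calendar time better, so the likely loss is a few points at most. Correlation within Glow groups and window-specific effects are the parts that alternation does not remove.

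**What to change.** In Section 7.2, replace the concluding claim with a statement such as: 289 analysable women per arm give 85% power at d = 0.25 and 67% at d = 0.20 if outcomes are independent.

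Add a short table of power and detectable effect over a stated ICC range. It should use the actual number of study women per Glow group and per provider-window, which the trial database can supply, and a design effect that reflects providers alternating arms. The levels assumed should match those fitted for Aim 1; Section 7.5 names clustering levels only under Aim 3.

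Covariate adjustment may regain some of the loss. Credit it only through an explicit assumption about the share of variance explained.

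The cost is a few sentences and one table. Enrolment, conduct and analysis do not change. The downside is a slightly less favourable stated figure.

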## **7.3 Inclusion of Women and Minorities**

As this study compares the effect of two models of enhanced prenatal care, we are, by necessity, restricting participant enrollment to women of reproductive age. We have selected 10 clinical sites which serve a racially/ethnically diverse patient population, many of whom have Medi-Cal coverage, to ensure that our findings are relevant to low-income women and women of color who are disproportionately affected by preterm birth, perinatal depressive and anxiety symptoms, and disrespectful prenatal care in the US.

## **7.4 Masking**

The study participant and the RRS who administers the screening and baseline interview will be aware of the participant's comparator assignment. Third trimester interviews, postpartum

interviews, and delivery medical record review will be conducted by a different staff person to ensure the assessor of the primary and secondary outcomes is masked to the participant's comparator assignment. There is one exception to this plan: if there is only one bilingual RRS on staff, they may need to complete third trimester and postpartum interviews with women they recruited and enrolled.

## 7.5 Data Analysis

Primary and secondary analyses will include all participants based on treatment assignment, according to intention-to-treat principles. We expect our experimental design with allocation of treatment sequence by provider to lead to minimal imbalance at the participant level. Nonetheless we will collect data and adjust for potential confounders. Confounding information will be collected via REDCap questionnaires at baseline, 3rd trimester, and postpartum. Medical records will be linked by participant name and date of birth and abstracted after delivery to obtain data for our clinical outcomes (preterm birth and gestational age at delivery) and covariates. Maternal comorbidities will also be recorded from the medical records. Adherence will be quantified as the number of prenatal care visits in each treatment model, as opposed to initial assignment. To assess the effectiveness of different durations of participation in either treatment, we will conduct a secondary analysis limited to 1) participants who have attended at least one group or individual care session (after randomization) and 2) participants who have attended at least one group or individual care session (after randomization). For all analyses, we will first examine descriptive statistics, check modeling assumptions, and present effect estimates along with associated confidence intervals. Data analysis will be conducted while masked to treatment assignment.

**Aim 1 Hypothesis:** Women assigned to Glow/GC will have greater reduction in depressive (**1°**) and anxiety (**2°**) symptom severity at 3 months postpartum (1° time point) and in the 3rd trimester (2° time point) than women assigned to CPSP/IC.

**Aim 1 Analyses:** We will compare changes in depressive (PHQ-9) and anxiety (GAD-7) symptom severity from baseline to three months postpartum and 3rd trimester. The multivariate analyses will follow an analytic plan similar to that of Aim 1, using linear mixed models to assess primary and secondary outcomes. We will conduct separate analyses comparing symptom exacerbation from baseline to 3rd trimester and baseline to 3 months postpartum. **Exploratory analyses (1a):** Previous work among pregnant women found rates of elevated depressive symptoms were 19.9% and 17.1% for Black and Latina women, respectively, compared to 9.5% of White women. We will explore the disparities in maternal mental health for Black and Latina women in our sample. Exploratory Aim 2a will follow the same analysis plan as 1a.

**Aim 2 Hypothesis:** Women assigned to Glow/GC will report more person-centered care (**1°**), respectful care (**2°**), and prenatal care satisfaction (**2°**) than women assigned to CPSP/IC, at 3 months postpartum (1° timepoint) and in the 3rd trimester (2° timepoint).

**Aim 2 Analyses:** We will use quantitative and qualitative methods to assess patient perceptions of person-centered care, respectful care, and satisfaction with care. The quantitative analysis will follow methods similar to those described in Aim 1, using linear mixed models for the PCPC and PCMC-US, MORi, and PCSS numeric outcomes. **Exploratory analyses (2a)** will follow the same plan above for the Black and Latina subgroups. **For Aim 2b**, in-depth interviews will focus on experiences of respectful and disrespectful care during the current pregnancy or in the past, experiences of racism in care or in other settings, and barriers/enablers of accessing care or services in their family/social network. The study will generate digital audio recordings and

transcripts encrypted when in transit. Data will be entered, coded, memoed, and organized using the Dedoose software program, which allows for open coding, theoretical memoing, and detailed conceptual matrixing of transcript and memo data within and across participants. Sorting functions allow for cross-group comparison by code or characteristic and for establishing a system of inter-coder reliability. We will store all data on a secure server at UCSF, accessible only to the investigative team via password-protected, encrypted computers.

**Aim 3 Hypotheses (exploratory):** Women assigned to Glow/GC will have lower rates of preterm birth (**primary (1°)**) and will give birth at higher gestational ages (**secondary (2°)**) than women assigned to CPSP/IC.

**Aim 3 Analyses:** We will describe simple differences in proportions of preterm birth and mean gestational age by treatment group. We will examine models comparing treatment assignment to Glow/GC versus CPSP/IC including the covariates, using logistic mixed models (for preterm birth) and linear mixed models (for gestational age), with clustering by practice and provider. We will examine assumptions of normality for the gestational age outcome, and deviations from linearity for covariates. **Exploratory subanalyses (3a):** We will explore preterm birth rates and gestational age at delivery among Black and Latina participants in each treatment arm, to examine whether Glow/GC and CPSP/IC may be more or less effective in these subgroups. These aims will be exploratory in nature, as we do not anticipate having a sufficient sample to have high power to test our hypotheses in these groups. We will assess effectiveness within subgroups based on race/ethnicity and language and report the p-value for interaction.

We will begin to code data immediately after the first phase of interviews are completed, in bimonthly data meetings that will include interview staff and co-investigators. We will take extensive notes during meetings to document emergent concepts and themes for codebook development. Codes will be developed mirroring the topics outlined in interview guides, which we will develop prior to study initiation. Regular data analysis meetings will create a constructive dialogue that both triangulate the quantitative and qualitative data collected in Aim 2. While reviewing qualitative data, we will note reoccurring themes (open coding). While completing open coding, we will write theoretical and methodological memos consistent with qualitative analysis methodologies. We will finalize a codebook and code and enter all data into Dedoose. We will review selected transcripts to check for inter-coder reliability. Staff will maintain the coding database and produce outputs for analysis and generate data summaries.

*Missing outcomes and covariates:* As baseline data will be collected at time of treatment assignment, and clinical outcomes will be obtained from medical record review, we do not estimate substantial missing data for Aim 3. We plan to reduce missing data for Aims 1 and 2 through our retention plan. We will record all reasons for study withdrawal and missing data. Participants lost-to-follow up will undergo medical record review for the outcomes of preterm birth and gestational age. Our mixed model analyses offer robust protection against data that are missing at random. We will assess missing data across study covariates and time points and use multiple imputation if it is appreciable. Pregnancies that end in miscarriage, abortion or fetal death prior to 20 weeks gestation will not be included in analysis.

*Heterogeneity of treatment effect (HTE):* We will assess if the effectiveness of Glow/GC compared with CPSP/IC differs by practice or patient characteristics through interaction analyses. Pre-specified analyses of treatment heterogeneity include: complications of pregnancy, parity, race/ethnicity, provider type (CNM, MD, NP). We will also conduct exploratory analyses on additional covariates (social support, site, size of practice or location, prior experiences of racism) to assess treatment differences. HTE will be assessed using interactions between

treatment assignment and each proposed effect modifier tested with a cut-point of ( $p < .10$ ) for HTE.

*Avoidance of bias:* The use of randomization of treatment initiation within practices allows us to minimize the risks of confounding and selection bias. More efficient designs with less susceptibility to bias are unfortunately not feasible in this study, as the treatment is administered at the practice level and needs to be incorporated without substantial interruption to clinical processes. To enhance generalizability of the study, we are recruiting from a diverse low-income patient population including English- and Spanish-speakers, with study staff and all assessment tools available in both languages. While we cannot mask treatment assignment to providers, participants or study staff, we will make every effort to ensure equivalent study procedures across both groups. Chart review and data analysis will be performed by study staff masked to treatment assignment to reduce ascertainment bias.

